#### Usual care

Participants in the usual care arm will not be offered either the OEP or FAME programmes. They will be free to participate in any other exercise as they would if they were not participating in the trial.

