### Outcome measures

The primary and secondary outcome measures have been chosen to reflect the needs of participants (e.g. functional outcomes, falls, confidence, quality of life, participant costs), of commissioners of exercise services in primary care and policy makers (e.g. physical activity, falls, NHS costs).

The primary outcome will be the proportion reaching the recommended physical activity (PA) target of at least 30 minutes of activity of moderate intensity on at least 5 days each week, measured using the CHAMPS, PASE and PHONE_FITT questionnaires. While measures will be taken at 0, 6, 12, 18 and 24 months after the intervention, our primary analysis will be of 12 month data, as this is the time when the effect of the intervention is expected to be maximal, as seen in a previous evaluation of the OEP in New Zealand [37].

The secondary outcomes will include:

(1) The direct health benefits: i.e. functional and psychological status, the rate of falls (the major safety outcome measure), the number and nature of falls, and fear of falling,

(2) Stage of change, self-efficacy for exercise and physical self-perception (self-esteem relative to the physical domain), which includes measurement of perceived importance (the degree to which participants value their physical condition, body image and physical strength) to inform predictors of exercise adherence and continuation, and participants' judgement of the value or importance of physical activity,

(3) Health - related quality of life and Quality adjusted life years (QALYs) [38],

(4) The NHS and private (participant) costs of each exercise programme, and possible cost offsets, identified from a comparison of health and social service utilisation of participants in all groups during the study period.

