### Statistical methods

Characteristics of participants and practices will be compared descriptively at baseline. Comparisons between treatment arms will be made using random effects models to allow for clustering between practices. Linear regression models will be used for continuous outcome variables, logistic models for binary outcome variables (in particular the primary endpoint, namely attainment of recommended exercise level at 12 months after the intervention), and Poisson or negative binomial models for data on rate of falls. The assumptions for using each model will be checked and analyses adjusted accordingly. All analyses will be undertaken, adjusted (a) for variables used for minimisation (centre, deprivation and practice size), (b) for baseline values of the outcome measure, and (c) for baseline variables which differ to a clinically significant extent between groups. Differential effects of the intervention by age, sex and baseline activity levels will be assessed for the primary outcome measures by adding terms for the interaction between age, sex and baseline activity levels and treatment arm to the regression models.

Multilevel models will be applied to take account of clustering at the practice level (applicable to all arms of the study) and practitioner effects which will apply to differing extents in the OEP arm (due to the effectiveness of different PSIs) and FaME arm (due to the effectiveness of different PMs). Analyses as recommended by Roberts [70] and Walwyn and Roberts [71] (2009) will be applied for this purpose.

While the primary endpoint will be attainment of recommended exercise levels at 12 months, we will investigate the profile of exercise attainment at all time points (0, 6, 12, 18 and 24 months post intervention). We will carry out repeated measures analysis using generalised estimating equations which account for the intra-participant dependency of the repeated measures. In particular we will investigate evidence for differences in effect of the interventions at the different time points.

As the study consists of two intervention arms and one control arm, primary analysis will consist of comparing each intervention group with the control group. No formal adjustment of p-values will be made, since the sample size has been specifically designed to test each intervention separately.

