The economic analysis will adopt standard techniques of economic appraisal [72]. The measure of effectiveness will be mean differences in QALY scores at the end of follow up after adjustment for baseline values, estimated in an analysis of covariance. If statistically significant differences between groups are found, incremental cost effectiveness ratios will be calculated to show the extra cost incurred per QALY gained. Comparisons will be conducted between the usual care group and each type of exercise programme, and between the two interventions, using group means of follow-up QALY values after adjusting for baseline levels. The impact of uncertainties in the estimation of costs and outcome variables will be explored using one way and probabilistic sensitivity analysis. Bootstrap methods will be used to represent uncertainty of estimates, either for constructing confidence intervals or probability curves.

Sensitivity analyses will investigate the cost-effectiveness of the interventions for people with different levels of physical activity, health status and health related quality of life at baseline. Secondary cost-effectiveness analyses will be conducted using physical activity and other outcomes as the measures of effectiveness.

Missing outcome data will be assumed to be "missing at random" (MAR), conditional on key predictors of "missingness" (in particular baseline values of the response variable, treatment arm, and measures of compliance post randomisation) Multiple imputation of outcome variables will be carried out using these predictors of "missingness" [73]. A further sensitivity analysis will be carried out where all who do not report their exercise levels will be assumed to be non-exercisers.

The full analysis set will comprise all randomised participants for whom one post-baseline assessment of the primary outcome measure is available. The per-protocol set will comprise all randomised participants who are deemed to have no protocol violations. CACE analysis will be carried out [74].); this seeks to estimate the difference between compliers in the intervention groups with those who would have complied in the non-intervention group. The safety set will be all randomised participants who undertake at least one OEP session or FaME class.

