### Risks

Participants will complete a health questionnaire at recruitment which is sent to their GP to confirm exclusion criteria, prior to commencement of either exercise programme. Previous evaluation of the OEP showed significant reductions in falls and injuries [31] No adverse effects occurred in previous evaluations of either the OEP or FAME programmes [32]. Safe exercise guidelines will be followed, pre-exercise assessment will be conducted and exercise intensity and difficulty will be increased with caution to minimise the risk of injury. All participants and their general practitioners will be informed of the potential risk of injury from any exercise programme in the information documents provided for participants and practices, so that consent is obtained with full knowledge of such risks.

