### Adverse events

An adverse event (AE) is any unfavourable and unintended sign, symptom, syndrome or illness that develops or worsens during the period of observation in the trial. This includes:

(1) Exacerbation of a pre-existing illness.

(2) Increase in frequency or intensity of a pre-existing episodic event or condition.

(3) Condition detected or diagnosed after the intervention even though it may have been present prior to the start of the study.

(4) Continuous persistent disease or symptoms present at baseline that worsen following the start of the study.

A Serious Adverse Event (SAE) is any adverse event occurring following study mandated procedures, having received the OEP or FaME programmes or usual treatment that results in any of the following outcomes:

(1) Death

(2) A life-threatening adverse event

(3) Inpatient hospitalisation or prolongation of existing hospitalisation

(4) A disability/incapacity

(5) A congenital anomaly in the offspring of a participant

Important medical events that may not result in death, be life-threatening, or require hospitalisation may be considered a serious adverse event when, based upon appropriate medical judgment, they may jeopardize the participant and may require medical or surgical intervention to prevent one of the outcomes listed in this definition.

All adverse events will be assessed for seriousness, expectedness and causality. All adverse events will be recorded and closely monitored until resolution, stabilisation, or until it has been shown that the study intervention is not the cause.

Participants will be asked to contact the trial site immediately in the event of any serious adverse event. The Chief Investigator shall be informed immediately and shall determine seriousness and causality in conjunction with any treating medical practitioners. A serious adverse event that is deemed directly related to or suspected to be related to the trial intervention will be reported to the ethics committee.

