## Discussion

The ProAct65+ trial is a primary care based exercise intervention for older people with wide inclusion criteria. The pragmatic trial design replicates the approach taken in successful primary care trials in New Zealand [37,63] and differs from the majority of trials which focus on falls reduction in selected groups by having continuation of physical activity as its primary outcome.

The problems that we anticipate are: 1) biases in recruitment, with those already exercising at a relatively high level being more likely to volunteer for this trial; 2) limited retention of recruits to the study, which we hope to minimise by relatively frequent but brief contact with participants after the end of the exercise programmes; 3) variation in 'doses' of exercise promotion, which we hope to avoid through our quality assurance processes; and 4) an increase in falls risk, as in previous studies [37], which we will counter through training of staff, risk reduction and risk management programmes.

Because the trial will document the levels of activity of participants, which can be compared with population norms, and the number screened, the number who are ineligible and the number who refuse, its findings will be generalisable. The findings will therefore be important for informing policy on exercise promotion and falls prevention amongst older people. They will be relevant to older people and to policy makers working in health, social care and leisure arenas, health and social care commissioners and providers, leisure providers and charities and voluntary organisations working with older people.

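### The safety set excludes the whole usual care arm and every exercise-arm non-starter, so an analysis run on it has no randomised comparator, and no analysis set is named for the planned falls comparison

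*Protocol article*

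**What the plan says.** The analysis sets are defined at the end of Statistical methods. The sentence on safety reads: "The safety set will be all randomised participants who undertake at least one OEP session or FaME class". Under Usual care the article says: "Participants in the usual care arm will not be offered either the OEP or FAME programmes".

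Other sections treat safety as a matter for all three arms:

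- Outcome measures lists, among the secondary outcomes, "the rate of falls (the major safety outcome measure").
- Adverse events defines a serious adverse event as one that follows study procedures, "having received the OEP or FaME programmes or usual treatment".
- Ascertainment of outcomes has falls recorded in self-completed diaries, and these are issued in every arm.
- Statistical methods says: "Comparisons between treatment arms will be made using random effects models to allow for clustering between practices". For falls it specifies "Poisson or negative binomial models for data on rate of falls".

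No sentence says which analysis set the falls model or the adverse event summaries will use.

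Two statements bear on prior risk. Risks says: "No adverse effects occurred in previous evaluations of either the OEP or FAME programmes [32"]. Discussion lists among the anticipated problems "an increase in falls risk, as in previous studies [37"].

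**The concern.** A safety population should let the reader judge whether the intervention causes harm. In people aged 65 and over, falls, hospital admissions and deaths will occur in every arm. A count among exercisers alone cannot separate harm from background rate; only the contrast with usual care can. The definition makes membership depend on exercising, which usual care participants are not offered, so that contrast is lost in any analysis that uses the set.

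The definition also selects after randomisation within the exercise arms. People who never start may be frailer or less well than those who do, and usual care has no corresponding group to remove. The remaining exercisers are then no longer comparable with usual care as randomised.

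This matters here because the article names falls as its main safety outcome and itself expects that falls risk might rise.

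**Working it through.** **Planned numbers (Sample size section).** The article's figures reproduce.

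- Individually randomised size, for 14.6% vs 4.9%, 90% power and 5% two-sided. The mean proportion is (0.146 + 0.049)/2 = 0.0975 and the difference is d = 0.097. n = [1.96·√(2 × 0.0975 × 0.9025) + 1.2816·√(0.146 × 0.854 + 0.049 × 0.951)]² / 0.097² = 194.5, so 195. With the continuity correction, n/4 × [1 + √(1 + 4/(n·d))]² = 214.6, so 215, as stated.
- Design effect: 1 + (32 − 1) × 0.01 = 1.31. Then 215 × 1.31 = 281.65, so 282.
- Attrition of 30%: 282/0.70 = 402.9, so 403 per arm.
- Three arms: 3 × 403 = 1,209.

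**Applying the safety set rule to each arm.**

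| Arm | Planned | In the safety set as written |
|---|---|---|
| OEP | 403 | at most 403 (non-starters removed) |
| FaME | 403 | at most 403 (non-starters removed) |
| Usual care | 403 | 0 |
| Total | 1,209 | at most 806 |

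The usual care share removed is 403/1,209 = 33% of all participants and 100% of the control arm. The article gives no expected number of non-starters, so 806 is an upper limit.

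**Setting the sections side by side.**

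1. The serious adverse event definition includes events under usual treatment. The safety set has no member in whom such an event could be counted. These two sections conflict.
2. The falls rate is called the major safety outcome, yet the set labelled for safety cannot supply a falls rate for usual care. This is a poor fit rather than a contradiction, because the falls model is described separately and is not tied to the safety set.
3. The full analysis set does include usual care, but it requires one post-baseline assessment of the primary outcome, a physical activity measure. The first follow-up is at 24 weeks. A usual care participant who dies or withdraws before then, and so provides no such assessment, belongs to neither set. The full analysis set is therefore not a ready substitute for safety.

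**Prior risk statements.** Risks reports no adverse effects in previous OEP or FaME evaluations. Discussion cites source 37 for an increase in falls risk, and Outcome measures describes source 37 as an earlier OEP evaluation in New Zealand. As worded, the three do not fit together. Whether the cause is a wrong citation or a real finding cannot be told from the article.

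**The case against.** The strongest reply is that the falls comparison does not depend on the safety set. Falls are a secondary outcome, diaries are kept in all arms, and Statistical methods plans Poisson or negative binomial models within its between-arm comparisons. This stands. A reader might infer from the label attached to the falls rate that falls will be analysed on the safety set, and so cannot be compared between arms. The article does not say so. Even on that set, OEP and FaME could be compared with each other.

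A second reply is that which set serves which outcome is normally left to the statistical analysis plan, which is not shown. This stands as regards silence about the falls model. It does not cover the definition itself, which the article states outright and which leaves out the control arm if followed.

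A third reply is that a safety set defined by exposure is a common convention, so leaving out non-starters is a choice and not an error. That is fair in part. The plain fault is the missing usual care arm. But simply adding usual care while still requiring a first session in the exercise arms would set a selected group against an unselected one.

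A fourth reply is that adverse event recording is not equal across arms. OEP mentors complete an adverse event form, and FaME instructors record feedback and reasons for drop-out. No equivalent regular contact is described for usual care. This stands, and it limits what the fix can deliver for non-serious events.

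Finally, the conflict over prior falls risk is a separate matter and does not support the point about the safety set.

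**Conclusion.** The point holds in a limited form. As written, the safety set contains 0 of 403 planned usual care participants and at most 806 of 1,209 overall, and it removes exercise-arm non-starters. Any adverse event or safety analysis run on it lacks a randomised comparator, which conflicts with the article's own serious adverse event definition. The between-arm falls comparison is planned and feasible, but its analysis set is not named and the safety set could not serve for a contrast with usual care.

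The conclusion assumes that allocation is followed, so that no usual care participant takes part in either programme, and that recruitment meets the planned 403 per arm. The absence of a control arm does not depend on the second assumption. A separate statistical analysis plan may name the sets for falls and adverse events, but it could restore usual care to the safety set only by departing from the published definition.

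The inconsistency on prior falls risk is visible in the text and carries less weight. Nothing can be said here about what the cited source found.

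**What to change.** Replace the safety set sentence with one that defines the safety population, for falls and serious adverse events, as all randomised participants analysed by allocated arm, usual care included. Name this population for the falls rate model, with each programme compared against usual care. Keep participants who took part in one or more OEP sessions or FaME classes as a descriptive exposed subset of the two exercise arms.

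State that between-arm safety comparisons will rest on the diaries and on serious adverse events. Non-serious events are likely to be recorded more closely in the exercise arms, through mentor forms and instructor records, and should be reported descriptively with that caveat. Serious events partly depend on participants contacting the site. The hospital admissions that the diaries record in all groups, checked against primary care records where participants consent, give a common source for part of them.

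Separately, reconcile Outcome measures, Risks and Discussion on what earlier evaluations showed about falls, and correct the citation if that is the cause.

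The cost is a sentence or two in the analysis section and an edit to the risk text. No sample size figure changes, and the falls diaries are already planned for every arm. The one small downside is the unequal recording of non-serious events, which redefining the set does not cure.

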### Protocol violations

Participants who are randomised to the OEP or FaME programmes who do not undertake any of the OEP programme or attend any FaME classes will be deemed to be protocol violations.

### Risks

Participants will complete a health questionnaire at recruitment which is sent to their GP to confirm exclusion criteria, prior to commencement of either exercise programme. Previous evaluation of the OEP showed significant reductions in falls and injuries [31] No adverse effects occurred in previous evaluations of either the OEP or FAME programmes [32]. Safe exercise guidelines will be followed, pre-exercise assessment will be conducted and exercise intensity and difficulty will be increased with caution to minimise the risk of injury. All participants and their general practitioners will be informed of the potential risk of injury from any exercise programme in the information documents provided for participants and practices, so that consent is obtained with full knowledge of such risks.

### Adverse events

An adverse event (AE) is any unfavourable and unintended sign, symptom, syndrome or illness that develops or worsens during the period of observation in the trial. This includes:

(1) Exacerbation of a pre-existing illness.

(2) Increase in frequency or intensity of a pre-existing episodic event or condition.

(3) Condition detected or diagnosed after the intervention even though it may have been present prior to the start of the study.

(4) Continuous persistent disease or symptoms present at baseline that worsen following the start of the study.

A Serious Adverse Event (SAE) is any adverse event occurring following study mandated procedures, having received the OEP or FaME programmes or usual treatment that results in any of the following outcomes:

(1) Death

(2) A life-threatening adverse event

(3) Inpatient hospitalisation or prolongation of existing hospitalisation

(4) A disability/incapacity

(5) A congenital anomaly in the offspring of a participant

Important medical events that may not result in death, be life-threatening, or require hospitalisation may be considered a serious adverse event when, based upon appropriate medical judgment, they may jeopardize the participant and may require medical or surgical intervention to prevent one of the outcomes listed in this definition.

All adverse events will be assessed for seriousness, expectedness and causality. All adverse events will be recorded and closely monitored until resolution, stabilisation, or until it has been shown that the study intervention is not the cause.

Participants will be asked to contact the trial site immediately in the event of any serious adverse event. The Chief Investigator shall be informed immediately and shall determine seriousness and causality in conjunction with any treating medical practitioners. A serious adverse event that is deemed directly related to or suspected to be related to the trial intervention will be reported to the ethics committee.

### Informed consent

Written informed consent will be obtained from all participants. The decision regarding participation in the study is entirely voluntary. The researcher will emphasize to potential participants that consent regarding study participation may be withdrawn at any time without penalty or affecting the quality or quantity of their future medical care, or loss of benefits to which the participant is otherwise entitled. No trial-specific interventions will be undertaken before informed consent has been obtained.

### Ethical and organisational review

Ethical approval has been granted to the trial from Nottingham Research Ethics Committee 2 (application number 08/H0408/72). National Health Service (NHS) Research & Development (R&D) approval has been granted by NHS Nottinghamshire County and Westminster, Brent, Hounslow and Barnet PCTs, and will be sought from other relevant PCTs as practices are recruited to the study.

